## CSPS.com

### Clinical Study Protocol Change

### Version 1.2 to 1.3

The first four columns of this table identify the location of the changes in version 1.3 of the protocol.

| Page                        | Chapter         | Ver 1.1 (deletions strike-through)                                                                                                                                                                                                                                                                    | Ver 1.2 (additions in bold)                                                                                                                                                                                                                                                                           |
|-----------------------------|-----------------|-------------------------------------------------------------------------------------------------------------------------------------------------------------------------------------------------------------------------------------------------------------------------------------------------------|-------------------------------------------------------------------------------------------------------------------------------------------------------------------------------------------------------------------------------------------------------------------------------------------------------|
| Cover page                  |                 |                                                                                                                                                                                                                                                                                                       | Version 1.3: 22 February, 2016                                                                                                                                                                                                                                                                 |
| All other pages
(Header) |                 | CSPS.com
Version 1.2: 24 February, 2014                                                                                                                                                                                                                                                            | CSPS.com
Version 1.3: 22 February, 2016                                                                                                                                                                                                                                                            |
| 4                           | Study
period | October 2013 to March 2017                                                                                                                                                                                                                                                                            | October 2013 to March 2018                                                                                                                                                                                                                                                                            |
| 24                          | 10.2            | The subject enrollment period lasts until target sample size is met. This period is planned to last from October 2013 to March 2016.
Study period lasts until 1 year after the first observation day of the last subject enrolled. This period is planned to last from October 2013 to March 2017. | The subject enrollment period lasts until target sample size is met. This period is planned to last from October 2013 to March 2017.
Study period lasts until 1 year after the first observation day of the last subject enrolled. This period is planned to last from October 2013 to March 2018. |

---

**Study of Antiplatelet Combination Therapy  
for Ischemic Stroke Patients with High Risk of  
Recurrence**

CSPS.com

(Cilostazol Stroke Prevention Study. *Combination*)

---

**ABBREVIATIONS AND DEFINITIONS**

|                         |                                                                                                                                                                                                                                                                                                                                                                             |
|-------------------------|-----------------------------------------------------------------------------------------------------------------------------------------------------------------------------------------------------------------------------------------------------------------------------------------------------------------------------------------------------------------------------|
| Evaluated events:       | Death, ischemic stroke, intracerebral hemorrhage, subarachnoid hemorrhage, transient ischemic attack (TIA), myocardial infarction, other vascular events (aortic dissection or rupture; pulmonary thrombosis; heart failure, angina pectoris, or occlusive arteriosclerosis requiring hospitalization), revascularization (e.g., coronary artery, aorta, peripheral artery) |
| Observation completion: | Observation is complete when a subject meets the criteria for discontinuation/completion or when 1 year has elapsed from the initiation of observation for last subject enrolled                                                                                                                                                                                            |
| Observation period:     | The period from the start to completion of the observations.                                                                                                                                                                                                                                                                                                                |
| Duration of morbidity:  | Period from the most recent noncardioembolic ischemic stroke to the start of observations                                                                                                                                                                                                                                                                                   |
| Descriptive statistics: | Number of subjects, mean, standard deviation, minimum, median, maximum                                                                                                                                                                                                                                                                                                      |
| GUSTO                   | Global Utilization of Streptokinase and t-PA for Occluded Coronary Arteries Trial                                                                                                                                                                                                                                                                                           |
| mRS                     | Modified Rankin Scale                                                                                                                                                                                                                                                                                                                                                       |

## **1. PREFACE**

This statistical analysis plan describes methods of summary and analysis with the purpose of providing the data required to prepare the report for this clinical study. It was prepared based on study protocol version 1.2, dated 2014/02/24 (CSPS.com).

## **2. STUDY OBJECTIVES AND ENDPOINTS**

### **2.1 Study objectives**

To examine the efficacy and safety of dual antiplatelet therapy (DAPT) including cilostazol (Pletaal OD Tablet® & reg.) in comparison with single antiplatelet therapy (SAPT) excluding cilostazol for secondary prevention of ischemic stroke in high-risk patients for stroke

### **2.2 Efficacy evaluation**

#### **2.2.1 Primary endpoint**

The following will be the primary endpoint.

- Recurrence of symptomatic\* ischemic stroke ("ischemic stroke" hereafter), with symptoms lasting for at least 24 hours

\* Symptoms continue for at least 24 hr after ischemic stroke onset.

#### **2.2.2 Secondary endpoints**

The following are the secondary endpoints.

- Any stroke (ischemic stroke, intracerebral hemorrhage, subarachnoid hemorrhage)
- Intracerebral hemorrhage or subarachnoid hemorrhage
- Ischemic cerebrovascular disorder [ischemic stroke or transient ischemic attack (TIA)]
- Death from any cause
- Stroke (ischemic stroke, intracerebral hemorrhage, subarachnoid hemorrhage), myocardial infarction, or vascular death
- All vascular events: stroke, myocardial infarction, and other vascular events [e.g., aortic dissection or rupture; pulmonary embolism; heart failure, angina pectoris, or occlusive arteriosclerosis requiring hospitalization; and revascularization (e.g., coronary artery, aorta, peripheral artery)]

### **2.3 Safety evaluation**

The following will be the safety endpoints.

- Adverse events and adverse drug reactions
- Severe or life-threatening hemorrhage (GUSTO criteria)

### 3. STUDY DESIGN

[figure not shown]

#### Observation schedule

| Evaluation items \ Timepoint                               | Date of onset | Enrollment | Start of observation | Month 1   | Month 3 | Month 6 | Month 12 | Every 6 months thereafter | End of observation (*) |
|------------------------------------------------------------|---------------|------------|----------------------|-----------|---------|---------|----------|---------------------------|------------------------|
| Informed consent                                           | ← ○           |            |                      |           |         |         |          |                           |                        |
| Enrollment                                                 |               | ○          |                      |           |         |         |          |                           |                        |
| Observation status                                         |               |            |                      | ○         | ○       | ○       | ○        | ○                         | ○                      |
| Patient characteristics                                    | ← ○           |            |                      |           |         |         |          |                           |                        |
| Degree of independence in activities of daily living (mRS) |               |            | ○                    | ○         | ○       | ○       | ○        | ○                         | ○                      |
| Study drug administration/compliance                       |               |            | ○                    | ○         | ○       | ○       | ○        | ○                         | ○                      |
| Drugs other than study drug                                |               |            | ○                    | ○         | ○       | ○       | ○        | ○                         | ○                      |
| Blood pressure                                             |               |            | ○                    | ○         | ○       | ○       | ○        | ○                         | ○                      |
| Head MRI                                                   | ← ○           |            |                      |           |         |         |          |                           |                        |
| Head MRI (T2* WI)                                          | ← △ →         |            |                      |           |         |         |          |                           |                        |
| Head MRA                                                   | ← △ →         |            |                      |           |         |         |          |                           |                        |
| Carotid artery imaging                                     | ← △ →         |            |                      |           |         |         |          |                           |                        |
| Laboratory test (blood)                                    | ← ○ →         |            |                      | ← ..... → |         |         |          |                           |                        |
| Laboratory test (urine)                                    | ← ○ →         |            |                      | ← ..... → |         |         |          |                           |                        |
| Chest x-ray                                                | ← ○ →         |            |                      | ← ..... → |         |         |          |                           |                        |
| ECG                                                        | ← ○ →         |            |                      | ← ..... → |         |         |          |                           |                        |
| Adverse events                                             |               |            | ← ..... →            |           |         |         |          |                           |                        |

○ Required item △ Optional item ← ..... → As required

\* Observation is complete when a subject meets criteria for discontinuation/completion, or when 1 year has elapsed from initiation of observation for last subject enrolled.

#### **4. TARGET SAMPLE SIZE AND RATIONALE**

We assumed an annual recurrence rate of 4% in the monotherapy group based on data from the EVEREST study and the aspirin monotherapy group in the JASAP study. We also assumed a 30% decrease in relative recurrence risk (in other words, an annual recurrence rate of 2.8%) in the DAPT group with cilostazol. The number of subjects required was calculated at 1,688 per group using the methods described by Lakatos et al  in our main analytical method of the log-rank test (conditions were assumed relapse rates for each group, a 2.5 year enrollment period, a maximum 3.5 year observation period,  $\alpha=0.05$ , and a statistical power of 80%). This results in a total target sample size of 4,000 (2,000 per group), assuming an annual dropout rate of 5% during the study period.

#### **5. ANALYSIS SETS**

The efficacy and safety analyses will use the intent-to-treat (ITT) analysis set.

##### **ITT analysis set**

The ITT analysis set is defined as the population of all randomized subjects. The subjects in this set belong to one of the treatment groups to which subjects were randomized, regardless of the drug they were actually administered.

The analysis set will be reexamined before database lock.

#### **6. DATA ANALYSIS CONSIDERATIONS**

##### **6.1 Software**

SAS release version 9.2 or later (SAS Institute, Cary, NC) will be used in the analysis.

##### **6.2 Data conversions and derivations**

###### **6.2.1 Age**

The subject's age at the time of informed consent (derived from date of birth and informed consent date indicated in database) will be used.

###### **6.2.2 Body Mass Index (BMI)**

BMI will be calculated based on the subject's height and weight at the time of the preliminary examination using the following formula.

$$\text{BMI (kg/m}^2\text{)} = \text{weight (kg)} / \{\text{height (m)}\}^2$$

### **6.2.3 Duration of morbidity**

The number of days from the most recent noncardioembolic ischemic stroke to the start of observations (first day of observations – day of ischemic stroke onset) will be calculated.

### **6.2.4 Observation period (person-years)**

For each group, the sum of the observation periods for the individual subjects will be determined, and the number of person-years will be calculated using 365.25 days for 1 year.

The observation period (observation end date - observation start date) will be the number of days from the first observation day to the last observation day (day subject meets the criteria for discontinuation or completion, or 1 year from start of observations for final subject enrolled).

### **6.2.5 Evaluated events**

The number of days from the first day of observations until onset (date of evaluated event onset - observation start date) will be calculated for the following evaluated events.

Death, ischemic stroke, intracerebral hemorrhage, subarachnoid hemorrhage, transient ischemic attack (TIA), myocardial infarction, other vascular events [aortic dissection or rupture; pulmonary thrombosis; heart failure, angina pectoris, or occlusive arteriosclerosis requiring hospitalization; revascularization (e.g., coronary artery, aorta, peripheral artery)]

## **6.3 Handling of timepoints**

Results for blood pressure and degree of independence in activities of daily living (mRS) for timepoints between treatment allocation and 10 days after observation completion will be included in the analysis.

When summarizing the data for blood pressure and degree of independence in activities of daily living (mRS) according to observation timepoint, a range of dates is defined for use as each timepoint, regardless of the observation timepoint indicated in the case report form (Table 6-3). The observation start date is designated day 0, and the day before the observation start date is designated day -1. If multiple evaluation values are observed for a given timepoint, the value obtained closest to the specified date will be used. If the values are equally divergent from the specified date, the latest value will be used.

Table 6-3: Ranges of examination timepoints used in statistical analysis

| Timepoint                       | Specified
Day *1 | Range Used (day)                     |
|---------------------------------|--------------------------------|--------------------------------------|
| Day before
observation start | -1                             | *3 up to -1 *2 |
| 1 month                         | 30                             | 16 to 44 (± 2 weeks)                 |
| 3 months                        | 91                             | 63 to 119 (± 4 weeks)                |
| 6 months                        | 183                            | 127 to 239 (± 8 weeks)               |
| 12 months                       | 365                            | 309 to 421 (± 8 weeks)               |
| 18 months                       | 548                            | 492 to 604 (± 8 weeks)               |
| 24 months                       | 731                            | 675 to 787 (± 8 weeks)               |
| 30 months                       | 913                            | 857 to 969 (± 8 weeks)               |
| 36 months                       | 1,096                          | 1,040 to 1,152 (± 8 weeks)           |
| 42 months                       | 1,278                          | 1,222 to 1,334 (± 8 weeks)           |
| 48 months                       | 1,461                          | 1,405 to 1,517 (± 8 weeks)           |

\*1: Specified day calculated using 1 month =  $365.25/12 = 30.4375$

\*2: Including 0 if preliminary examination performed

\*3: Handling of exceedingly old data will be examined before analysis.

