## Observation schedule

| Time point
Evaluation items               | (Date of onset) | Enroll-ment | Start of obser-vation | Month 1   | Month 3 | Month 6 | Month 12 | Every 6 months there-after | End of obser-vation (*) |
|----------------------------------------------|-----------------|-------------|-----------------------|-----------|---------|---------|----------|----------------------------|-------------------------|
| Informed consent                             | ← ○             |             |                       |           |         |         |          |                            |                         |
| Enrollment                                   |                 | ○           |                       |           |         |         |          |                            |                         |
| Observation status                           |                 |             |                       | ○         | ○       | ○       | ○        | ○                          | ○                       |
| Patient characteristics                      | ← ○             |             |                       |           |         |         |          |                            |                         |
| Degree of independence in daily living (mRS) |                 |             | ○                     | ○         | ○       | ○       | ○        | ○                          | ○                       |
| Study drug administration/ compliance        |                 |             | ○                     | ○         | ○       | ○       | ○        | ○                          | ○                       |
| Drugs other than study drug                  |                 |             | ○                     | ○         | ○       | ○       | ○        | ○                          | ○                       |
| Blood pressure                               |                 |             | ○                     | ○         | ○       | ○       | ○        | ○                          | ○                       |
| Head MRI                                     | ← ○             |             |                       |           |         |         |          |                            |                         |
| Head MRI (T2* WI)                            | ← △ →           |             |                       |           |         |         |          |                            |                         |

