## 10.2. Study period

The subject enrollment period lasts until target sample size is met. This period is planned to last from October 2013 to March 2017.

Study period lasts until 1 year after the first observation day of the last subject enrolled. This period is planned to last from October 2013 to March 2018.

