## 10.7 Other safety endpoints

### Degree of independence in activities of daily living (mRS)

Evaluate as one of following 7 levels according to Japanese Modified Rankin Scale (Japanese Guidelines for Management of Stroke 2009). A frequency distribution will be determined for each treatment group and timepoint, and a shift table will be prepared for the values at each timepoint before and after the start of the observation for each treatment group.

0. No symptoms at all
1. No significant disability despite symptoms: able to carry out all usual duties and activities
2. Slight disability: unable to carry out all previous activities, but able to look after own affairs without assistance
3. Moderate disability: requiring some help, but able to walk without assistance
4. Moderate to severe disability: unable to walk without assistance and unable to attend to own bodily needs without assistance
5. Severe disability: bedridden, incontinent and requiring constant nursing care and attention
6. Dead

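### SAP Table 6-3 gives many end-of-observation mRS and blood pressure readings no timepoint, although SAP 6.3 says they are included

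*Supplement*

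**What the plan says.** The observation schedule (protocol v1.3 and SAP 3) marks mRS and blood pressure as required at the end of observation. Protocol v1.3, 5.3, ends observation when any event listed in 6.3.3 occurs, when drug withdrawal exceeds 4 weeks, or on other withdrawal, and asks for the necessary observations at that point. SAP 7 repeats these criteria.

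SAP 6.3 says mRS and blood pressure results "for timepoints between treatment allocation and 10 days after observation completion will be included in the analysis". It then states that, for summaries by timepoint, "a range of dates is defined for use as each timepoint, regardless of the observation timepoint indicated in the case report form". Table 6-3 lists a pre-start row and rows for months 1, 3, 6 and every 6 months from 12 to 48. If two readings share a range, the one nearest the specified day is kept, and the later one in a tie.

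SAP 10.6 and 10.7 report only by these timepoints. For mRS, "A frequency distribution will be determined for each treatment group and timepoint", with shift tables; for blood pressure, descriptive statistics and a figure. SAP 6.4 imputes nothing.

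The SAP was finalised in March 2014 against protocol v1.2 and is listed as unchanged. Protocol v1.3, 10.2, moves the end of enrolment to March 2017 and says of the study period: "This period is planned to last from October 2013 to March 2018".

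**The concern.** The plan requires an end-of-observation reading, says it is included, and then sorts readings by a rule that has no place for many of them. The end date is set by an event, a discontinuation or the common closing date, so it need not fall near a routine visit. The form's visit label cannot rescue the reading because the rule disregards it, and no last-value summary is defined elsewhere.

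mRS is the only disability scale the trial collects. The tables in SAP 10.7 would omit a sizeable part of the final disability readings, including some taken because a stroke ended observation. Blood pressure summaries lose final values in the same way.

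**Working it through.** **1. Reproduce Table 6-3.** Specified day = months × 30.4375, rounded; range = specified day ± 14 days (month 1), ± 28 (month 3) or ± 56 (month 6 onward). All ten specified days (30, 91, 183, 365, 548, 731, 913, 1,096, 1,278, 1,461) and all ten ranges, from 16–44 to 1,405–1,517, reproduce exactly. The half-widths equal the visit tolerances in protocol 6.2.4.

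**2. Count the uncovered days.** Up to day 1,517, these days lie in no range:

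- 1–15 (15 days), 45–62 (18), 120–126 (7), 240–308 (69)
- 422–491 (70), 605–674 (70), 788–856 (69), 970–1,039 (70)
- 1,153–1,221 (69), 1,335–1,404 (70)

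The sum is 527 of 1,517 days (34.7%).

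**3. Length of the table.** Taking 1 October 2013 to 31 March 2018 gives 1,642 days; enrolment to 31 March 2017 gives 1,277 days. Days 1,518–1,642 (125 days) have no row. If everyone stays to closing and accrual is uniform, 125 / 1,277 = 9.8% of patients end after day 1,517.

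**4. Closing-date readings only.** End days then spread evenly over 365–1,642, which is 1,278 days. The uncovered days are 70 + 70 + 69 + 70 + 69 + 70 = 418 in the gaps plus 125 after day 1,517, so 543 / 1,278 = 42.5%.

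**5. Add early exits.** End day = the smaller of the administrative end (1 year + uniform accrual) and an exponential early-exit time, simulated for 2 million patients per scenario. The plan's sample-size text gives stroke rates of 4% and 2.8% a year (mean 3.4%) and 5% dropout, so 8.4% a year in total. The rates of 11%, 20% and 30% are assumptions to show the range. Accrual of 3.5 years is the calendar in protocol v1.3, 10.2; 2.5 years is what protocol 11.1 and 11.4.1 still state.

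| Early exit per year | All end readings in no window (3.5-year accrual) | Early-exit readings only (3.5-year) | Ending after day 1,517 (3.5-year) | All end readings in no window (2.5-year) | Early-exit readings only (2.5-year) |
|---|---|---|---|---|---|
| 0% | 42.5% | – | 9.8% | 38.2% | – |
| 8.4% | 40.5% | 34.9% | 6.9% | 37.4% | 34.1% |
| 11% | 40.0% | 34.8% | 6.2% | 37.2% | 34.0% |
| 20% | 38.4% | 34.5% | 4.3% | 36.5% | 33.8% |
| 30% | 37.1% | 34.1% | 2.8% | 35.9% | 33.5% |

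Taking the reading 0 to 10 days after the end date changes the all-readings share by at most 0.4 percentage points.

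**6. Displacement inside a window.** A patient seen on day 365 whose observation ends with a stroke on day 400 has two readings in the 309–421 range, and the nearest-day rule keeps the one from day 365. As an extreme illustration, suppose every routine visit falls exactly on its specified day. Then every end reading in the later half of a window is displaced: 14 + 28 + 8 × 56 = 490 further days, or 527 + 490 = 1,017 of 1,517 (67%). Closing the gaps alone would therefore not solve the problem.

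**7. After the change.** With an end-of-observation row, every reading obtained at the end assessment has a place. For the extra visit row, 54 × 30.4375 = 1,643.6, giving specified day 1,644 and range 1,588–1,700.

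**The case against.** The strongest reply is that the gaps are deliberate. The ranges equal the protocol's visit tolerances, so every routine visit held on time up to 48 months is captured, and leaving out-of-tolerance readings out of a per-visit table is a legitimate choice. That stands, and it is why the windows should be kept. It does not explain why a reading that the schedule requires and SAP 6.3 includes has no row.

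A reader might infer that the gaps selectively remove readings taken because something went wrong. The figures do not support this: event and dropout readings are missed at about 35%, less often than closing-date readings at about 38–43%. The windows depend on the day and not the arm, so no between-arm bias is shown either.

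A reader might also infer that a stroke or death on, say, day 270 vanishes from the trial. It does not. The primary and secondary endpoints (SAP 9), adverse events (10.1 to 10.4) and bleeding (10.5) do not use Table 6-3. mRS and blood pressure are summarised descriptively, without a test, and neither is a named safety endpoint in protocol 9 or SAP 2.3.

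Finally, the percentages depend on assumptions. If sites enter the last routine visit as the final reading, the loss is smaller. If early accrual was slower than uniform, fewer patients end after day 1,517. The table was also long enough for v1.2; the shortfall arose only with v1.3.

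**Conclusion.** The point holds as a defect in the descriptive mRS and blood pressure reporting. It is more than missing detail, because a stated rule leaves out readings that the plan requires and says it will include. With uniform accrual and a reading taken at the end date, about 35% of event- or dropout-triggered end readings and about 36–43% of all end readings fall in no timepoint. Roughly 7–10% of patients could end after the last row on the v1.3 calendar, from the plan's own stroke and dropout rates to no early exit; heavier early exit lowers this. Some end readings inside a window are also displaced by a routine reading closer to the specified day. The structural facts can be read directly from the table; the percentages are only as firm as the accrual and timing assumptions. Nothing here touches the primary result or any event-based analysis.

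**What to change.** Before database lock, amend SAP 6.3 and Table 6-3 as follows, leaving the existing per-visit windows unchanged.

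- **Add an *End of observation* row.** It takes the reading obtained at the end-of-observation or discontinuation assessment: the one closest to the observation end date and no later than 10 days after it. Earlier routine visits are not carried forward. A row defined simply as the last value after the start would let an early visit stand in for a missing final one, in tension with SAP 6.4. Show a death that ends observation as mRS 6, a category SAP 10.7 already has.
- **Add a 54-month row:** specified day 1,644, range 1,588 to 1,700.
- **Add one output to SAP 10.6 and 10.7:** a baseline-to-end mRS shift table and a blood pressure summary by arm, split by reason for ending (event, other discontinuation, study closure) and labelled as having varying follow-up times.

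The cost is two table rows and one descriptive summary. The schedule already requires the data, so sites do nothing extra. The drawback is that the end row mixes readings taken soon after an event with routine readings at up to about 4.5 years; the split by reason and the label are there to make that visible. Deaths after a first non-fatal event has ended observation need not appear in this row, and the table should say so.
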